### Recruitment Plan

Participants will be recruited through a combination of clinical and community-based outreach strategies to ensure a diverse sample of adults with CMP. Primary recruitment will occur through an orthopedic specialty clinic located in the Southeastern United States. Potential participants will be identified through direct referrals from clinicians or may self-refer after viewing recruitment materials displayed in the clinic. To supplement clinic-based recruitment, we will implement community outreach strategies designed to engage individuals with CMP who may not be actively seeking specialty care. These strategies will include the distribution of digital and print advertisements across local community centers and libraries. Targeted social media campaigns (eg, Facebook and Instagram [Meta Platforms]) will further expand recruitment reach. All advertisements will include a brief study description, eligibility criteria, and a link to a secure online screening form. Interested individuals will be directed to complete a brief web-based prescreening questionnaire to determine initial eligibility. Those who appear eligible will be contacted by study staff for a structured telephone interview to confirm inclusion and exclusion criteria.

### AE Reporting and Harms

Participant safety and data integrity will be monitored on an ongoing basis by the PI and designated study team members. Any reported events, whether physical, psychological, or behavioral, will be documented in a standardized case report form and evaluated for severity, duration, and potential relationship to the study intervention. The PI will assess each AE for relatedness and seriousness and determine whether the event qualifies as an unanticipated problem involving risk to participants.

Any AE or unanticipated problem involving risk to participants will be reported in accordance with the local IRB policies and applicable regulatory requirements. Nonserious but study-related AEs will be recorded and reviewed regularly by the study team to identify any emerging patterns that could indicate risks associated with the intervention or trial procedures. Participants who experience distress or negative effects related to the intervention (eg, heightened anxiety) will be provided with appropriate support. All documentation of AEs will be maintained in a secure, confidential manner and reviewed periodically to ensure prompt and appropriate response.

### Patient and Public Involvement Statement

Patients and the public were not involved in the design, conduct, reporting, or dissemination plans of this research.

### Interventions

Participants in the 2 active treatment arms (MB and MB+DP) will attend 4 weekly, 30-minute, manualized mindfulness training sessions. Each session will be delivered in person by a PhD-level interventionist. In addition to the in-session mindfulness practice, all participants will be assigned daily at-home mindfulness practice throughout the 4-week intervention period. The at-home mindfulness practice will be a 15-minute, audio-recorded mindfulness practice recorded by a clinician and sent to participants via email. Each participant in the active treatment groups will receive a 15-minute audio recording that corresponds to the specific mindfulness practice style of the group to which they were randomized.

Each session will follow a consistent structure. The first session will begin with a 5-minute introduction to the intervention. In Sessions 2 through 4, the initial 5 minutes will be used to review participants’ experiences with their at-home mindfulness practice. All sessions will then include a 15-minute guided mindfulness practice and conclude with 10 minutes of therapist-led inquiry and reflective discussion. This structure is informed by established and empirically supported brief mindfulness intervention models [43]. To ensure treatment fidelity, all sessions will be audio-recorded. A study supervisor will review session recordings and provide regular supervision, ensuring adherence to the treatment manual and consistency in intervention delivery across participants. The specific elements of each session in both programs are described in Table 1.

**Table 1. T1:** Content and practice overview of each session of mindful breathing (MB) and mindful breathing+direct pointing (MB+DP) active treatment groups.

Program session	MB^a^	MB+DP^b^	Total session duration
1	Brief introduction and pain psychoeducation (5 minutes) Formal practices: Mindfulness of breath (15 minutes) Therapeutic processing (10 minutes)	Brief introduction and pain psychoeducation (5 minutes) Formal practices: Mindfulness of breath (10 minutes) 5 minutes of direct pointing instruction Therapeutic processing (10 minutes)	30 minutes
2	Brief welcome + review of at-home practice (5 minutes) Formal practices: Mindfulness of breath (15 minutes) Therapeutic processing (10 minutes)	Brief welcome + review of at-home practice (5 minutes) Formal practices: Mindfulness of breath (10 minutes) 5 minutes of direct pointing instruction Therapeutic processing (10 minutes)	30 minutes
3	Brief welcome + review of at-home practice (5 minutes) Formal practices: Mindfulness of breath (15 minutes) Therapeutic processing (10 minutes)	Brief welcome + review of at-home practice (5 minutes) Formal practices: Mindfulness of breath (10 minutes) 5 minutes of direct pointing instruction Therapeutic processing (10 minutes)	30 minutes
4	Brief welcome + review of at-home practice (5 minutes) Formal practices: Mindfulness of breath (15 minutes) Therapeutic processing (10 minutes)	Brief welcome + review of at-home practice (5 minutes) Formal practices: Mindfulness of breath (10 minutes) 5 minutes of direct pointing instruction Therapeutic processing (10 minutes)	30 minutes

a MB: mindful breathing.

b MB+DP: mindful breathing+direct pointing.

#### Mindful Breathing (MB)

Participants assigned to the MB group will engage in a focused attention mindfulness practice adapted from validated brief mindfulness protocols [43,44]. During the 15-minute guided practice, participants will be instructed to maintain attention on the breath, particularly sensations at the nostrils and abdomen, and to gently return their focus to the breath when distracted by thoughts, emotions, or bodily sensations. When pain arises, they will be guided to acknowledge it nonjudgmentally, without resistance or elaboration, before returning their attention to the breath.

#### Mindful Breathing+Direct Pointing (MB+DP)

Participants assigned to the MB+DP group will receive the same initial instructions as the MB group for the first 10 minutes of practice. During this time, foundational mindfulness skills are cultivated to support receptivity to the DP instruction. In the final 5 minutes of the guided practice, the therapist will deliver DP instructions, an introspective, contemplative technique derived from Mahamudra and Dzogchen traditions [22,23]. DP aims to shift attention from the contents of awareness (eg, pain and thoughts) to the nature of awareness itself [22,23]. Instructions will guide participants to experientially investigate the spacious, nonconceptual qualities of awareness, often described in classical sources as possessing inherent clarity and bliss [22,23]. The DP phase is designed to induce a transient, self-transcendent state in which rigid identification with self-referential content (eg, “I am in pain”) may dissolve.

#### Waitlist Control (WLC)

The WLC group was included to provide a reference for the natural progression of symptoms in the absence of additional intervention. While this group allows for assessment of change over time relative to no treatment, it does not control for nonspecific factors such as attention, expectancy, or facilitator contact. Participants assigned to the WLC group will not receive any active intervention during the initial 4-week study period but will complete all study assessments on the same schedule as those in the treatment arms. Specifically, they will undergo baseline evaluation and complete identical outcome measures, such as self-reported self-transcendent state, acute pain ratings, EEG, and fNIRS, at time points matched to Sessions 1 and 4 of the intervention groups. They will also complete the full set of follow-up assessments at 1 week, 1 month, and 3 months postintervention to evaluate potential naturalistic changes in clinical outcome variables over time. Following the final assessment, participants in the waitlist group will be offered the opportunity to participate in a 2-hour MBI for chronic pain.

### Measures

Outcomes will be evaluated at two primary timescales: (1) during and immediately surrounding the mindfulness training sessions to assess mechanistic changes, including self-reported self-transcendence and psychophysiological responses, and (2) at baseline and follow-up intervals to examine the durability of clinical effects. Psychophysiological data (EEG and fNIRS), along with session-specific self-report measures, will be collected during the first and final training sessions (Sessions 1 and 4) to assess within-participant changes over the course of the intervention (see Table 2). Broader clinical outcomes, including pain interference, pain catastrophizing, and sleep disturbance, will be assessed remotely via online surveys at baseline and again at 1-week, 1-month, and 3-month postbaseline to evaluate the persistence of any treatment-related improvements (Table 3).

**Table 2. T2:** State survey: overview of measures and corresponding measurement time points.

Measure	Target concept	Session 1	Session 2	Session 3	Session 4
NADA-S^a^	Self-transcendence	✓			✓
MPoD^b^	Decentering	✓			✓
Pain intensity (single item)	Pain intensity	✓			✓
EEG^c^	Frontal midline theta power	✓			✓
fNIRS^d^	Fronto-temporal-parietal cortical proxy of DMN^e^ activity; cerebral cortex	✓			✓

a NADA-S: Nondual Awareness Dimensional Assessment–State.

b MPoD: Metacognitive Processes of Decentering Scale.

c EEG: electroencephalogram.

d fNIRS: functional near-infrared spectroscopy.

e DMN: default mode network.

**Table 3. T3:** Trait survey: overview of measures and corresponding measurement time points.

Measure	Target concept	T0^a^	T1^b^	T2^c^	T3^d^
BPI^e^ – Functional Interference	Functional Interference	✓	✓	✓	✓
NIH HEAL CDE^f^ Demographics	Demographic Information	✓			
BPI-PI^g^	Pain Intensity	✓	✓	✓	✓
Physical function	Physical function	✓	✓	✓	✓
PCS^h^	Pain catastrophizing	✓	✓	✓	✓
PHQ-2^i^	Depression	✓	✓	✓	✓
GAD-2^j^	Anxiety	✓	✓	✓	✓
PROMIS^k^ Sleep Disturbance – Short Form 6a	Sleep	✓	✓	✓	✓

a T0: 1-week pretreatment (Baseline).

b T1: 1-week post treatment.

c T2: 1-month post treatment.

d T3: 3-month post treatment.

e BPI: Brief Pain Inventory.

f NIH HEAL CDE: The Helping to End Addiction Long-term Initiative Common Data Elements.

g PI: Pain intensity

h PCS: Pain Catastrophizing Scale.

i PHQ-2: Patient Health Questionnaire 2-item.

j GAD-2: Generalized Anxiety Disorder 2-item.

k PROMIS: Patient-Reported Outcomes Measurement Information System.

### Primary Outcome

#### Primary Self-Report Outcome

The self-transcendent state will be assessed immediately before and after the first and final treatment sessions using the state version of the Nondual Awareness Dimensional Assessment (NADA-S). This validated 3-item measure captures momentary fluctuations in nondual awareness. Two items assess reductions in self-salience, and one assesses the presence of bliss. All items are rated on an 11-point numeric rating scale ranging from 0 (“not at all”) to 10 (“extremely”).

#### Primary Psychophysiological Outcomes

Frontal midline theta power will be measured by EEG. In Sessions 1 and 4, participants in the active treatment groups (MB and MB+DP) will complete psychophysiological data collection during a 5-minute resting baseline prior to treatment and throughout the 15-minute mindfulness practice. During the same sessions, participants in the WLC group will undergo a 5-minute resting baseline followed by a 15-minute time-matched control period. During all psychophysiological assessments, EEG will be continuously recorded from 10 midline scalp sites (Fz, F3, F4, FC1, FC2, FCz, Cz, CP1, CP2, and PZ) using an active sensor cap with Ag-AgCl electrodes (actiCap GmbH). In addition, vertical electrooculograms will be recorded. All recordings will be collected with an actiCHamp amplifier (Brain Products GmbH). Data will be acquired at a sampling rate of 500 Hz, a resolution of 0.489 µV and an amplification cutoff of 140 Hz, with impedances kept below 10 kilohms.

Connectivity in a validated fronto-temporal-parietal cortical proxy of DMN activity (ie, connectivity in-between channels belonging to the medial prefrontal cortex and the left and right MTG and STG, left and right posterior temporoparietal lobe, left and right temporoparietal junction will be measured by fNIRS during a 5-minute resting baseline period before treatment and during the 15-minute mindfulness practice. Hemodynamic responses to neuroactivation via oxy-, deoxy-, and total hemoglobin changes in the cerebral cortex will be measured with the NIRx NIRSport 2, a user-friendly, modular, and robust wireless fNIRS platform. The automated signal optimization algorithm ensures optimal signal quality before a measurement is started. Once data are being recorded, oxygenated hemoglobin and hemoglobin concentration changes can be visualized in real-time in several display modes. In addition, high-end whole-head visualizations are immediately available.

#### Acute Clinical Outcome

Acute pain intensity will be measured immediately before and after Sessions 1 and 4 using a single-item numeric rating scale: “How intense is your pain right now?” Responses are scored on an 11-point scale from 0 (“no pain”) to 10 (“worst pain imaginable”).

### Tertiary and Secondary Outcomes

#### Tertiary Clinical Outcomes

The following pain-related outcomes will be assessed using validated instruments from the Helping to End Addiction Long-term Initiative (NIH HEAL) Common Data Elements (CDE) battery at pretreatment and posttreatment time points (see Table 4): Brief Pain Inventory, Patient-Reported Outcomes Measurement Information System (PROMIS) Physical Functioning Short Form 6b, Brief Pain Catastrophizing Scale (PCS), Patient Health Questionnaire-2 (PHQ-2), Generalized Anxiety Disorder 2-Item Scale (GAD-2), and PROMIS Short Form v1.0–Sleep Disturbance 6a.

**Table 4. T4:** Schedule of enrollment, interventions, and assessments (SPIRIT [Standard Protocol Items: Recommendations for Interventional Trials] diagram).

**Description**	**Study phase**			In-lab **procedures**				Follow-**u**p **p**ost**-t**reatment		
	Enrollment	Baseline	Allocation	Week 1	Week 2	Week 3	Week 4	1-week	1-month	3-month
**Time point**	–T1^a^	T0^b^						T1^c^	T2^d^	T3^e^
**Enrollment**										
Eligibility form	✓									
Informed consent	✓									
MINI^f^	✓									
**Randomization**										
Allocation			✓							
**Study arm**										
MB^g^				✓	✓	✓	✓	✓	✓	✓
MB+DP^h^				✓	✓	✓	✓	✓	✓	✓
WLC^i^				✓			✓	✓	✓	✓
**Assessments**										
NADA-S^j^				✓			✓			
EEG^k^				✓			✓			
fNIRS^l^				✓			✓			
MPoD^m^				✓			✓			
Acute pain intensity				✓			✓			
At-home mindfulness practice (MB and MB+DP only)				✓	✓	✓	✓			
BPI^n^		✓						✓	✓	✓
Physical function		✓						✓	✓	✓
PCS^o^		✓						✓	✓	✓
PHQ-2^p^		✓						✓	✓	✓
GAD-2^q^		✓						✓	✓	✓
PROMIS^r^ sleep disturbance		✓						✓	✓	✓
Pain catastrophizing		✓						✓	✓	✓

a –T1: Enrollment activities

b T0: 1-week pretreatment (baseline).

c T1: 1-week posttreatment.

d T2: 1-month posttreatment.

e T3: 3-month posttreatment.

f MINI: Mini-International Neuropsychiatric Interview.

g MB: mindful breathing.

h MB+DP: mindful breathing+direct pointing.

i WLC: waitlist control.

j NADA-S: Nondual Awareness Dimensional Assessment-State.

k EEG: electroencephalogram.

l fNIRS: functional near-infrared spectroscopy.

m MPoD: Metacognitive Processes of Decentering.

n BPI: Brief Pain Inventory.

o PCS: Pain Catastrophizing Scale.

p PHQ-2: Patient Health Questionnaire 2-item.

q GAD-2: Generalized Anxiety Disorder 2-item.

r PROMIS: Patient-Reported Outcomes Measurement Information System.

#### Pain

Participants will self-report their pain intensity, treatments for pain relief, effectiveness of those treatments, and pain interference with the 14-item BPI. Statements include “Please rate your pain by indicating the one number that best describes your pain at its WORST in the past 24 HOURS” with an 11-point Likert-like scale (0=no pain, 10=pain as bad as you can imagine). Five items measure recent and immediate pain intensity. One item asks participants about their pain treatments, and the next immediate item asks how much relief the treatments offered (from 0% to 100%). The next 7 items measure pain interference in the participant’s daily life with an 11-point Likert-like scale (0=does not interfere, 10=completely interferes).

#### Physical Function

Participants will self-report their physical function with the PROMIS Physical Function (PROMIS Physical Functioning Short Form 6b) questionnaire [45]. The PROMIS Physical Function questionnaire is a 6-item measure using a 5-point Likert scale (5=not at all, 1=cannot do) with questions such as “Does your health now limit you in doing two hours of physical labor?” Other questions, such as “Are you able to do chores such as vacuuming or yard work?,” use a 5-point Likert scale (5=without any difficulty, 1=unable to do).

#### Pain Catastrophizing

Participants will be asked about their pain catastrophizing with the Brief Pain Catastrophizing Scale (PCS) [36]. The Brief PCS is a validated, 5-item questionnaire on which participants rate their thoughts and feelings about pain on a 5-point Likert scale, ranging from 0 (“Not at all”) to 4 (“All the time”). Statements include “It’s awful, and I feel that it overwhelms me.”

#### Depression

Depressive symptoms were measured using the Patient Health Questionnaire-2 (PHQ-2), a 2-item questionnaire that serves as a brief screener for depression [35]. The PHQ-2 prompts patients to reflect on their mood over the previous 2 weeks, asking them how often they experienced “little interest or pleasure in doing things” or felt “down, depressed, or hopeless.” A 4-point Likert scale ranging from 0 (not at all) to 3 (nearly every day) is used to report the frequency of depressive symptoms, and a total score is determined from summing these points together. A total score of 3 or greater supports the need for further screening and indicates an increased likelihood of major depressive disorder.

#### Anxiety

Anxiety symptoms were measured using the Generalized Anxiety Disorder 2-Item Scale (GAD-2), a 2-item screener for generalized anxiety disorder [46]. Similar to the PHQ-2, the GAD-2 asks patients about how often they experienced certain symptoms over the past 2 weeks, including “feeling nervous, anxious, or on edge” and “not being able to stop or control worrying.” Both items are scored using a 4-point Likert scale that spans from 0 (not at all) to 3 (nearly every day). Points from these 2 items are added together to calculate a total score, with a total score of 3 or above being suggestive of generalized anxiety disorder.

#### Sleep

Sleep disturbance was assessed with the PROMIS Sleep Disturbance Scale (PROMIS Short Form v1.0–Sleep Disturbance 6a), a 6-item questionnaire that evaluates a patient’s overall sleep experience [33]. The first item evaluates a patient’s sleep quality over the past 7 days. Responses are scored on a 5-point Likert scale ranging from 1 (very poor) to 5 (very good). The other 5 items ask about the depth and restfulness of a patient’s sleep over the past 7 days. Sample items include “My sleep was refreshing” and “I tried hard to get to sleep.” As with the first item, these responses are also scored on a 5-point Likert scale ranging from 1 (not at all) to 5 (very much).

#### Process Measures

Engagement with at-home mindfulness practice will be monitored using a Qualtrics-based tracking system. Each participant will receive a unique survey link embedded with their participant ID to record the frequency and duration of practice. At the beginning of Sessions 2, 3, and 4, participants will also self-report their adherence to at-home exercises, including at-home mindfulness practice duration and any notable experiences.

As a manipulation check, state mindfulness will be assessed using the Metacognitive Processes of Decentering (MPoD) scale [47] administered immediately before and after Sessions 1 and 4. The MPoD captures momentary shifts in decentering, a key psychological mechanism thought to mediate mindfulness-related outcomes.

Participants will receive modest financial compensation at the baseline assessment and 3 follow-up time points. These compensation procedures are designed to recognize participant contributions while maintaining ethical standards for noncoercive remuneration.

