Mindfulness-based interventions (MBIs) offer a promising means of disentangling chronic pain from the sense of self, thereby disrupting the maladaptive cycle that sustains the pain individuals endure [9]. Rather than providing mere distraction or placebo effects, mindfulness engages specific neural and psychological mechanisms that fundamentally alter pain perception and appraisal [15-17]. Central to this process is a reduction in self-referential processing, a shift supported by neuroimaging evidence showing decoupling between the thalamus and DMN hubs such as the precuneus and medial prefrontal cortex during mindfulness practice [9,15,18,19]. This decoupling may represent a loosening of the neural circuits that enmesh pain in the sense of self, facilitating a more open, present-centered awareness [9,15,18,19]. The Mindfulness-to-Meaning Theory deepens this perspective by suggesting that mindfulness initiates a recursive cycle of positive psychological processes, including decentering, attentional broadening, cognitive reappraisal, and savoring, that synergistically promote self-transcendent states [9]. These transient states, characterized by diminished self-salience and expansive positive affect (eg, awe, bliss, and compassion), weaken the cognitive and emotional enmeshment between the individual and their pain experience [9,20]. Through momentary dissolution of the subject-object dichotomy, self-transcendence can reduce the centrality of pain in consciousness and cultivate a renewed sense of meaning [9,20]. In this way, mindfulness-induced self-transcendence may not only reshape the brain’s functional architecture but may also reframe the lived experience of pain, offering a path toward relief that is both neurologically grounded and psychologically liberating [9].

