### Aims

To isolate the specific effect of DP to mindfulness-based pain relief, the Pointing Beyond project will randomize 173 adults with CMP into one of three groups: (1) 4 weekly 30-minute sessions of traditional mindful breathing (MB) instruction, (2) 4 weekly 30-minute sessions of MB combined with DP (MB+ DP) instruction, or (3) a waitlist control group (WLC). The specific aims are:

#### Aim 1

Evaluate between-group differences in changes in self-transcendence from Session 1 to Session 4 across the MB, MB+DP, and WLC groups, using a validated self-report instrument (state version of the Nondual Awareness Dimensional Assessment [NADA-S]; primary outcome) and 2 psychophysiological indices (secondary outcomes), including frontal midline theta activity (via electroencephalography [EEG]) [28,29] and a functional near-infrared spectroscopy (fNIRS) [31] derived proxy default mode network (DMN) activity.

#### Aim 2

Examine the associations among phenomenological and psychophysiological indices of self-transcendence by testing within- and between-session correlations between self-reported self-transcendent state (NADA-S), frontal midline theta activity (EEG), and fNIRS-derived proxy DMN activity across intervention sessions and study groups.

#### Aim 3

Determine whether increases in self-transcendence mediate treatment-related improvements in pain outcomes by testing indirect effects of group assignment (MB, MB+DP, and WLC) on (1) acute pain intensity at the end of Session 4 (secondary outcome) [32] and (2) pain-related outcomes (eg, functional interference) through 3-month follow-up (tertiary outcomes) [33-38], via changes in (1) self-reported self-transcendence (NADA-S), (2) frontal midline theta activity (EEG), and (3) fNIRS-derived DMN activity measured during Session 4, controlling for presession pain and baseline levels of the mediators.

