### Hypotheses

The following are our hypotheses:

#### Aim 1

We hypothesize that, from Session 1 to Session 4, both mindfulness groups (MB and MB+DP) will show greater increases in self-transcendence, indexed by higher NADA-S scores and greater frontal midline theta activity (EEG), and greater decreases in DMN activity, indexed by reduced fNIRS-derived fronto-temporal-parietal connectivity, compared to WLC group. We further hypothesize that MB+DP will produce larger increases in these phenomenological and neurophysiological indices of self-transcendence, and larger reductions in DMN activity, relative to MB alone.

#### Aim 2

We hypothesize that phenomenological and psychophysiological indices of self-transcendence will be significantly and coherently related across sessions and groups, such that a higher self-reported self-transcendent state (NADA-S) will be associated with greater frontal midline theta activity (EEG) and lower fNIRS-derived proxy DMN activity within sessions and across Sessions 1-4. We further hypothesize that these associations will be the strongest in the MB+DP group, intermediate in the MB group, and the weakest or absent in the WLC group, reflecting graded coupling between subjective experience and neural indices of self-transcendence as a function of mindfulness instruction type.

#### Aim 3

We hypothesize that treatment-related improvements in pain outcomes will be mediated by increases in self-transcendence and its psychophysiological correlates. Specifically, we expect that assignment to the mindfulness groups, particularly MB+DP, will be associated with lower acute pain intensity at the end of Session 4 and reduced pain-related functional interference through 3-month follow-up via (1) increases in self-reported self-transcendent state (NADA-S), (2) increases in frontal midline theta activity (EEG), and (3) reductions in fNIRS-derived proxy DMN activity measured during Session 4, controlling for presession pain and baseline levels of each mediator [39,40].

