Second, to enhance the clinical interpretability of the intervention effects, we added a waitlist control group. This adjustment was made prior to participant enrollment. Inclusion of this no-treatment comparison group provides a benchmark against which to evaluate the specific impact of the MBIs on both mechanistic and clinical outcomes, relative to the natural progression of symptoms in the absence of additional intervention. This control arm was designed to be half the size of each active treatment group (n=35), resulting in a total sample size of 173 and preserving a 2:2:1 randomization ratio. This total sample size (n=173) is consistent with a G*Power estimate for a 3 (group)×2 (time) mixed design, assuming a small effect (Cohen *d*=0.30), 80% power, and a Bonferroni-adjusted alpha of .0125 for 4 pairwise comparisons (ie, self-reported self-transcendence; 2 psychophysiological indices of self-transcendence, including frontal midline theta activity and DMN activity, and acute pain). Beyond these primary group-level effects, the planned sample size also supports Aims 2 and 3. Specifically, a G*Power analysis (2-tailed, *α*=.0167, corrected for multiple comparisons; power=0.80) indicated that 112 participants are sufficient to detect a moderate association (*r*=0.30) among phenomenological and psychophysiological indices of self-transcendence, well below the planned sample of n=173. Finally, this sample size is adequate for the planned mediation analyses; the parallel multiple-mediator model for acute pain includes 19 estimated parameters, yielding approximately 9.1 observations per parameter with n=173, consistent with the commonly cited 5‐10 observations per parameter convention.

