Several challenges warrant consideration. Capturing transient self-transcendent states during brief interventions requires sensitive instrumentation and careful interpretation. While fNIRS offers valuable ecological validity, its spatial resolution limits assessment of deeper DMN structures such as the posterior cingulate cortex. Moreover, ensuring fidelity in delivering nuanced practices such as DP necessitates skilled facilitators and robust supervision protocols. Despite these limitations, the study’s emphasis on real-time neural and experiential assessment in naturalistic settings enhances its translational relevance.

The Pointing Beyond project represents a theoretically grounded and methodologically rigorous effort to identify the specific mechanisms through which mindfulness produces pain relief. By isolating the contribution of direct pointing instruction, triangulating subjective and neurobiological indices of self-transcendence, and testing their mediating role in both acute and sustained pain outcomes, this trial directly contributes to the scientific understanding of the experiential and neural processes through which mindfulness relieves CMP.

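### Aim 3 tests self-transcendence as a mediator of pain relief without decentering (MPoD), a concurrently measured rival whose own effect on pain, if it has one, can be credited in part to NADA-S

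*Protocol article*

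**What the plan says.** The Aims section fixes the Aim 3 mediators. Indirect effects of group on acute pain at the end of Session 4, and on pain-related outcomes through 3-month follow-up, run "via changes in (1) self-reported self-transcendence (NADA-S), (2) frontal midline theta activity (EEG), and (3) fNIRS-derived DMN activity measured during Session 4". The adjustment set is also fixed: "controlling for presession pain and baseline levels of the mediators". The Hypotheses section states the claim to be tested, that "treatment-related improvements in pain outcomes will be mediated by increases in self-transcendence and its psychophysiological correlates".

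The Participants section sizes this model: "the parallel multiple-mediator model for acute pain includes 19 estimated parameters, yielding approximately 9.1 observations per parameter with n=173". It compares that ratio with a 5-10 "observations per parameter convention".

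Decentering appears in two other places. The Background says mindfulness starts a recursive cycle of processes, "including decentering, attentional broadening, cognitive reappraisal, and savoring, that synergistically promote self-transcendent states". The Process Measures section schedules the MPoD immediately before and after Sessions 1 and 4, the same moments as the NADA-S, and adds that "The MPoD captures momentary shifts in decentering, a key psychological mechanism thought to mediate mindfulness-related outcomes". The only use it gives the MPoD is as a manipulation check. Nowhere does the article enter the MPoD in the mediation analysis as mediator, covariate or sensitivity check.

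**The concern.** Randomisation protects the path from group to mediator. It does not protect the path from mediator to pain. On the article's own account, decentering is raised by mindfulness, promotes self-transcendence, and is itself thought to mediate outcomes. The Background also describes direct pointing as training deidentification with thoughts and sensations, so the MB+DP versus MB contrast may move decentering too.

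A variable that treatment moves, that raises NADA-S, and that also affects pain by its own route confounds the NADA-S-to-pain path. Adjusting for baseline mediators and presession pain does not remove this, because the confounding arises after randomisation. Theta and the fNIRS proxy do not stand in for decentering either, since the article offers them as indices of self-transcendence.

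The treatment comparisons of Aim 1 are unaffected. What is at stake is how a positive Aim 3 result may be read: as evidence for self-transcendence, or as evidence that cannot tell self-transcendence from a rival process already on the assessment schedule.

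**Working it through.** **1. The article's own figure.** 173/19 = 9.1 observations per parameter, as stated. The 19 are not itemised. One natural count with three mediators and two group contrasts reaches 19: 6 group-to-mediator paths + 3 mediator-to-pain paths + 2 direct paths + 3 baseline mediators + 1 presession pain + 4 residual variances. The stated size therefore fits a model without the MPoD.

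**2. The same count with MPoD as a fourth mediator.** 8 + 4 + 2 + 4 + 1 + 5 = 24, and 173/24 = 7.2. Adding all 6 residual covariances gives 30, and 173/30 = 5.8. Both lie inside the 5-10 convention at n=173. With 138 analysed the ratios are 138/24 = 5.8 and 138/30 = 4.6, so the larger version would fall below it.

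**3. Direction of the bias.** Work in within-arm SD units with a single treatment contrast. All of these values are assumptions: treatment raises decentering by 0.5 and self-transcendence by a further 0.3; decentering acts on pain at -0.3; self-transcendence has no effect on pain; k is the path from decentering to self-transcendence. With decentering omitted:

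- apparent NADA-S-to-pain path = -0.3 × k
- group-to-NADA-S path = 0.3 + 0.5 × k
- spurious indirect effect = the product of the two

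| k | apparent path to pain | group-to-NADA-S path | spurious indirect effect |
|---|---|---|---|
| 0 | 0 | 0.30 | 0 |
| 0.3 | -0.09 | 0.45 | -0.04 |
| 0.5 | -0.15 | 0.55 | -0.08 |
| 0.7 | -0.21 | 0.65 | -0.14 |

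Simulation gives the same values, and with decentering in the pain equation the apparent path returns to 0. If decentering's own effect on pain is set to 0 and self-transcendence truly acts at -0.3, omitting decentering leaves the path at -0.3 for every k. There is then no bias.

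**4. How often a false indirect effect would be declared for MB+DP versus MB.** Simulation inputs, all assumed unless noted:

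- Analysed arms 28/55/55 (WLC/MB/MB+DP). This takes planned arms of 35/69/69 and reverses the article's 25% inflation: 35/1.25 = 28, 69/1.25 = 55, total 138.
- MPoD shifts versus WLC of 0.4 (MB) and 0.7 (MB+DP).
- Decentering effect on pain -0.3; NADA-S effect on pain 0.
- MB+DP minus MB on NADA-S of 0.6 or 0.3. The article gives d=0.60 as its smallest preliminary effect and sizes on d=0.30.
- Joint significance of the group-to-NADA-S and NADA-S-to-pain paths, by ordinary least squares, at alpha .05 or .0167. The article uses .0167 for the Aim 2 correlations and states no alpha for mediation.

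Ranges are across repeat runs; columns are the within-arm NADA-S/MPoD correlation.

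| NADA-S difference, alpha | .3 | .5 | .7 |
|---|---|---|---|
| 0.6, .05 | 14-17% | 34-37% | 57-61% |
| 0.6, .0167 | 6% | 19% | 40% |
| 0.3, .05 | 6% | 12-15% | 22-24% |
| 0.3, .0167 | 1-2% | 5% | 9-10% |

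With MPoD in the pain equation the rate is 5% or less throughout. The simulation omits theta, the fNIRS proxy, presession pain and baseline mediators, so it illustrates the mechanism and does not reproduce the planned model.

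**5. Cost when NADA-S truly mediates.** With an effect of 0.3 SD, a NADA-S difference of 0.6 and alpha .05, power is about 80% without MPoD. With it, power is about 80%, 74% and 60% at correlations .3, .5 and .7.

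**The case against.** The strongest reply has four parts.

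- **The bias is conditional.** A reader might infer that decentering's effect on pain simply will be credited to self-transcendence. The article does not support that. The Background largely describes decentering as acting through self-transcendence, and under that route nothing is lost. The Process Measures wording is tentative, does not name pain, and does not assert a path that bypasses self-transcendence. This part stands in full.
- **The larger percentages need favourable inputs.** At the sizing effect of 0.30 and a corrected alpha the false rate is 10% or less. This stands, and it is why the whole range is shown.
- **Adjustment is not neutral.** The two scales are rated together, the Background calls the process recursive, and two of the three NADA-S items concern reduced self-salience, so the scales may overlap. If decentering is partly a consequence of self-transcendence, adjusting for it removes real mediated effect. It is tempting to allow the self-transcendence claim only if it survives MPoD adjustment, but the data cannot establish the order that such a rule needs.
- **The claim is milder than sole mediation.** The Discussion aims to "identify the specific mechanisms through which mindfulness produces pain relief", in the plural, and elsewhere self-transcendence is called a candidate mechanism. A reader might infer that the article claims self-transcendence alone carries the benefit; it does not say so.

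It can also be said that testing a chosen mediator set while using another scale as a manipulation check is legitimate, and that sensitivity analyses are often left to an analysis plan. The first is true, and there is no contradiction in the text. The second answers less here, because the article itself fixes the mediators, the covariates and a parameter count, and gives the MPoD one other role.

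**Conclusion.** The point holds in conditional form. Aim 3 leaves the NADA-S-to-pain path open to a measured, treatment-induced rival that neither randomisation nor baseline adjustment removes. The direction follows from the article's own theory once decentering has some effect on pain outside self-transcendence; without such an effect there is no bias. The size rests on assumed effects and correlations: false NADA-S mediation for MB+DP versus MB in roughly 15-60% of trials at d=0.6 and alpha .05, 6-24% at d=0.3 and alpha .05, and 1-10% at d=0.3 and alpha .0167, against 5% or less with MPoD included. This calls for a worthwhile and cheap improvement. It does not make the three-mediator model invalid.

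**What to change.** Keep the three-mediator model as the primary Aim 3 analysis. Prespecify a sensitivity model that adds post-Session-4 MPoD, adjusted for its Session 1 pre-session value, as a fourth parallel mediator in the pain equation, leaving the group-to-NADA-S equation unchanged. Report the NADA-S indirect effect with its interval from both models. If the estimate shrinks materially, describe the mediation as not separable from decentering. Do not tie the claim to statistical significance in the adjusted model, and say that concurrent ratings cannot settle which process comes first.

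The cost is analysis wording only, since the MPoD is already scheduled and recruitment is expected to run to May 2027. The sensitivity model has about 24 parameters instead of 19 (about 7.2 observations per parameter at n=173), and its NADA-S interval will be wider when the two scales correlate strongly, with power falling from about 80% to about 60% at a correlation of .7.
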